#### Secondary outcomes

3.5.2

Secondary outcomes will include biochemical, clinical, cognitive and gastrointestinal measures, to provide a broader assessment of the intervention’s effects beyond GM composition. All secondary clinical and biomarker outcomes will be considered exploratory in this pilot trial and will primarily provide feasibility metrics and effect-size estimates to inform a definitive RCT. In details:

a.   Biochemical analyses will include:Changes in zonulin (biomarker of intestinal permeability) assessed by measurement of fecal zonulin concentration (reported in ng/mL) using an ELISA kit.Changes in calprotectin (biomarker of intestinal inflammation) assessed by quantitative measurement of fecal calprotectin (reported in μg/g feces) using a validated immunoassay (ELISA or automated chemiluminescent assay) on stool sample.Assessment of EVs size (nanometers) and concentration (particles/mL) in plasma and saliva using nanoparticle tracking analysis (NTA) and transmission electron microscopy (TEM).Phenotyping of EVs in plasma and saliva through the analysis of EV-associated proteins, using fluorescent NTA (f-NTA), ELISA, and flow cytometry.a.   Functional-motor assessments will include:b.   Changes in Movement Disorder Society—Unified Parkinson’s Disease Rating Scale (MDS-UPDRS) parts II (motor aspects of daily living), III (motor examination), and IV (motor complications), a widely validated measure of PD progression (Goetz et al., 2007).c.   Changes in walking speed and gait-related spatiotemporal parameters by using a wearable inertial sensor device (G-sensor, BTS Bioengineering, Milan) (Zago et al., 2018), including:d.   Stride length (m), defined as the distance between two successive heel strikes of the same foot;e.   Stride length/height (%), the stride length normalized by subject height;f.   Cadence (steps/min), the number of steps taken per minute;g.   Propulsion (m/s^2^), the anterior–posterior acceleration during the swing phase of the lower limb;Changes in execution timing of Time Up and Go, a validated measure of mobility, balance, walking ability, and fall risk (Kleiner et al., 2018).Changes in Berg Balance Scale (BBS), a standardized tool for evaluating static and dynamic balance (Qutubuddin et al., 2005).Clinical-functional assessments will include:Changes in cognitive function through the administration of MMSE, MoCA, Frontal Assessment Battery (FAB), and clock-drawing tests, which are widely used to assess multiple cognitive domains (Folstein et al., 1975; Nasreddine et al., 2005; Bezdicek et al., 2017).Changes in depressive symptoms, measured with the Beck Depression Inventory-II (BDI-II), a 21-item self-report scale for depression severity (Steer et al., 1998).Changes in non-motor symptoms, assessed with MDS-UPDRS part I (non-motor daily living experiences) and the Non-Motor Symptoms Scale (NMSS) in PD (Van Wamelen et al., 2021).Changes in quality of life, measured with the Parkinson’s Disease Questionnaire (PDQ-39), which evaluates eight domains of daily functioning (Jenkinson et al., 1997).Gastrointestinal assessment will include:Changes in gastrointestinal function, measured through the administration of Gastrointestinal Symptom Rating Scale (GSRS) (Rusch et al., 2024; Kenna et al., 2021), the Bristol Stool Form Scale (Lewis and Heaton, 1997; O’Donnell et al., 1990), and the Digestion-Associated Quality of Life Questionnaire (DQLQ) (Beke et al., 2022).

### Adverse events

3.6

Although the interventions are non-pharmacological and are expected to pose minimal risk, adverse events that may occur will be those normally associated with standard clinical treatment for PD. For this protocol, an adverse event is defined as any unfavorable or unintended sign, symptom, abnormal laboratory result, or medical condition that arises during study participation, regardless of causality. Adverse events will be actively monitored throughout the intervention and follow-up, with specific attention to events potentially related to physical activity (e.g., falls and exercise intolerance) and to gastrointestinal symptoms (e.g., constipation and abdominal pain) potentially related to dietary changes. Participants will receive standardized instructions on safe exercise execution and on when/how to contact the study team. Exercise sessions will be supervised. All such events will be documented and reviewed by the principal investigator and the research team to assess severity and any link to study participation, with appropriate clinical management and follow-up until resolution or clinical stability.

### Data collection and management

3.7

All data will be systematically recorded in Research Electronic Data Capture (REDCap), a secure web-based application for building and managing online surveys and databases. Participants will be identified only by a unique study identification number (ID) to ensure anonymity; no personally identifiable information will be stored in the electronic database. Hard-copy linkages between participant IDs and contact details will be retained in a locked file cabinet within a secure office, with access restricted to designated members of the research team. Participant files and other source data—including questionnaires, original test reports, informed consent records, and all other study-related documents—will be retained for the maximum period permitted by institutional policy.

## Statistical analysis

4

Statistical analyses will be conducted using IBM Statistical Packages for Social Science Software (SPSS) version 23 (IBM Corp., Armonk, NY, United States) and R (R Foundation for Statistical Computing, Vienna, Austria) for microbiome-specific analyses. A *p*-value < 0.05 will be considered statistically significant for the prespecified primary analysis; multiplicity control will be applied where appropriate for exploratory high-dimensional microbiome analyses using false discovery rate procedures (e.g., Benjamini–Hochberg). Baseline characteristics will be summarized using descriptive statistics [mean ± standard deviation (SD) for normally distributed data, or as median with interquartile ranges (IQR) in case of asymmetric distributions]. Categorical variables will be expressed in terms of absolute frequencies and percentages. Comparisons across the four study groups will be conducted using statistical tests appropriate to the data type and distribution for outcomes assesses at a single time point (ANOVA or Kruskal-Wallis for continuous variables; Chi-square/Fisher’s for categorical variables). Given the longitudinal design (T0, T1, FU1, FU2), outcomes measured repeatedly over time will be analyzed using mixed-effects models to account for within-participant correlation. Analyses will be conducted primarily under an intention-to-treat principle; sensitivity analyses will assess the impact of missing data where relevant. For continuous outcomes, linear mixed-effects models will include fixed effects for time, diet, exercise, and their interactions (time × diet × exercise) (or time × trial arm), and a random intercept for participant. For non-normally distributed outcomes, appropriate transformations or generalized mixed models will be considered. The prespecified primary contrast will focus on the change from T0 to T1 in the combined intervention versus standard care (control); analyses including FU1 and FU2 will be considered secondary/exploratory and reported as durability/maintenance assessments. In addition, subgroup analyses will be conducted to explore potential heterogeneity of intervention effects by disease stage (I/II/III of H&Y), age group, and gender, where sample size permits, with results interpreted as exploratory. Sensitivity analyses will be conducted to assess the robustness of findings, including adjustment for prespecified covariates and assessment of protocol adherence where relevant.

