### Participants and eligibility criteria

3.2

The calculation of the sample size was not strictly required given the pilot nature of this study. Accordingly, the target sample size was primarily driven by feasibility considerations and the need to obtain precise effect-size estimates to inform a definitive RCT. However, to support the microbiome endpoint, we performed an *a priori* power assessment. Following the recommendations of Ferdous et al. (2022), we selected β-diversity as the primary endpoint to detect differences between groups in the composition of intestinal microbial species. Using G*Power version 3.1.9.7, assuming an effect size of (Cohen’s f) 0.25, a statistical power of 0.95 (1−β) and setting α to 0.05, we estimated the minimum required sample size. To account for expected attrition during the intervention and follow-up period (approximately 10%), the total sample size was increased to 80 participants (20 per arms). Participants will be recruited from Clinical Trial Centers for Parkinson’s Disease (RU1 - RU2) during routine clinical visits. A total of eighty (*n* = 80) participants meeting the following eligible criteria will be enrolled and randomly assigned to an intervention or to the control group:

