### Fecal microbiome processing, sequencing, bioinformatics, and statistical analysis

4.1

Fecal collection kits and detailed instructions will be provided to participants. Samples will be stored at −80 °C until processing. DNA will be extracted using the PowerSoil Pro DNA kit (Qiagen). For short-read profiling, the V4–V5 region of the 16S rRNA gene will be amplified using primers 515F and 926R with Illumina barcodes. For long-read profiling, the 16S-ITS-23S operon will be amplified with primers A515F and U2428R and PacBio barcodes to obtain amplicons > 3,500 bp. Sequencing of both short- and long-read libraries will be performed by the Sequencing Core at the University of Illinois at Urbana-Champaign (UIUC). Raw sequence data will be processed in the R statistical environment; DADA2, a bioinformatics pipeline, specifically developed for modeling and correcting amplicon sequencing errors (Callahan et al., 2016), will be used for quality assessment, length filtering, denoising high-quality reads into Amplicon Sequence Variants (ASVs) and chimera removal.

Given the complexity of the dataset, microbiome statistical analysis will be conducted using standardized and reproducible methodologies. α- and β-diversity analyses will be assessed at appropriate taxonomic levels, from phylum to genus, using the phyloseq package in R (McMurdie and Holmes, 2013). α-diversity will be estimated using indices such as Shannon, Simpson, and Faith’s phylogenetic diversity and between-group differences will be tested using appropriate non-parametric test (e.g., Kruskal-Wallis) for cross-sectional comparisons or generalized linear models adjusted for covariates. For longitudinal analyses across T0, T1, FU1, and FU2, mixed-effects models will be used where appropriate to account for repeated measures within participants. β-diversity will be quantified using distance metrics including Bray-Curtis, Jaccard, and weighted/unweighted Unifrac. The prespecified primary microbiome analysis will focus on Bray–Curtis β-diversity and will evaluate whether the change from T0 to T1 differs between the combined intervention (Group C) and standard care (Group D) using Permutational Multivariate Analysis of Variance (PERMANOVA). To account for the repeated-measures structure, permutation testing will be restricted within participants. FU1 and FU2 will be included in secondary/exploratory analyses of durability/maintenance.

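### For the mixed-model outcomes, T0 is a response with a free mean in each arm, so the combined-versus-control T0–T1 contrast forgoes the precision of baseline adjustment

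*Protocol article*

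**What the plan says.** Section 4 (Statistical analysis) of the protocol article treats baseline as one of the repeated measurements: "Given the longitudinal design (T0, T1, FU1, FU2), outcomes measured repeatedly over time will be analyzed using mixed-effects models". For continuous outcomes, "linear mixed-effects models will include fixed effects for time, diet, exercise, and their interactions (time × diet × exercise"), with the alternative "or time × trial arm), and a random intercept for participant". The comparison of interest is then named: "The prespecified primary contrast will focus on the change from T0 to T1 in the combined intervention versus standard care (control").

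Neither coding sets the T0 means equal across arms or enters the T0 value as a covariate. Adjustment appears only later in the section: "Sensitivity analyses will be conducted to assess the robustness of findings, including adjustment for prespecified covariates". The outcome's own baseline value is not named there.

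Two other places set the scope. Section 4.1 tests the primary endpoint outside this model, comparing Group C with "standard care (Group D) using Permutational Multivariate Analysis of Variance (PERMANOVA"). Section 3.5.2 says of the rest: "All secondary clinical and biomarker outcomes will be considered exploratory in this pilot trial". Section 3.2 gives as one driver of the sample size "the need to obtain precise effect-size estimates to inform a definitive RCT".

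**The concern.** Allocation is randomised 1:1:1:1 (section 3.4.1), so any difference between arms at T0 is chance. A model that gives each arm a free T0 mean subtracts that chance difference in full when it forms the T0–T1 contrast. A baseline-adjusted model subtracts only the part that T0 predicts, and its estimate is less variable.

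The outcomes concerned are the continuous secondary ones analysed by this model, such as zonulin, calprotectin, MDS-UPDRS, gait measures and PDQ-39, and α-diversity where the mixed model is used for it. At stake is the width of the effect-size estimates that this pilot is meant to hand to a definitive trial, from 20 participants per arm, or about 18 after the expected attrition.

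**Working it through.** **The plan's own figure.** The only sizing figure is 80 participants (20 per arm), for β-diversity, with f = 0.25, power 0.95, α = 0.05 and about 10% attrition. The G*Power test family and correlation are not stated. Assuming a within-between interaction with 4 groups, 2 times and correlation 0.5, N = 73; 73/0.9 gives 82 and 73 × 1.1 gives 81, close to 80. Nothing below depends on this.

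**Inputs.** n = 20 per arm (section 3.2), or 20 × 0.9 = 18 after attrition. The outcome SD is set to 1 and assumed equal at T0 and T1. The T0–T1 correlation ρ is not given, so it is varied from 0.3 to 0.9.

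**Step 1: what the planned contrast is.** The arm-by-time mean structure is saturated under either coding. With complete data the fitted means are the observed cell means, whatever the random intercept variance. The contrast is

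(mean T1 − mean T0 in C) − (mean T1 − mean T0 in D).

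Fitting the stated model to simulated complete data (4 arms × 20, 4 times) gave 0.017538, identical to the raw difference in mean change. The random intercept therefore does no baseline adjustment. In a simulated dataset with 10% dropout after T0, the model gave −0.138 and the completers' raw change −0.172. The identity is then only approximate, but the T0 means remain free.

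**Step 2: variances per participant.**

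- Planned (change): 2(1 − ρ)
- Baseline-adjusted: 1 − ρ²
- Ratio: (1 − ρ²) / [2(1 − ρ)] = (1 + ρ)/2
- Cost of estimating the slope: factor 1 + 1/(4n − 6) = 1 + 1/74 = 1.0135 at n = 20, about 1.4%

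The SE of C versus D is √(2 × variance / n).

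| ρ (assumed) | Planned variance | Adjusted variance | Ratio | Ratio with df cost | SE planned | SE adjusted | n per arm for planned model to match adjusted n = 20 |
|---|---|---|---|---|---|---|---|
| 0.3 | 1.40 | 0.91 | 0.65 | 0.66 | 0.374 | 0.304 | 30.4 |
| 0.5 | 1.00 | 0.75 | 0.75 | 0.76 | 0.316 | 0.276 | 26.3 |
| 0.7 | 0.60 | 0.51 | 0.85 | 0.86 | 0.245 | 0.227 | 23.2 |
| 0.9 | 0.20 | 0.19 | 0.95 | 0.96 | 0.141 | 0.139 | 20.8 |

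At 18 per arm the SEs go from 0.394 to 0.320, 0.333 to 0.291, 0.258 to 0.240, and 0.149 to 0.146.

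**Step 3: simulation check (4,000 replicates per ρ).** Variance ratios with T0 as covariate were 0.67, 0.76, 0.87 and 0.96. With a common T0 mean and ρ treated as known they were 0.66, 0.75, 0.86 and 0.95. Both agree with the formula.

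**Step 4: a common T0 mean with only a random intercept.** That model weights T0 by one correlation pooled over the four times. If the pooled value is 0.5 but the T0–T1 correlation is 0.7, the adjusted variance is 1 + 0.5² − 2 × 0.5 × 0.7 = 0.55. The ratio is 0.55/0.60 = 0.92 instead of 0.85, so about half of the gain is lost.

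**The case against.** The strongest reply is that nothing here is invalid. An arm-by-time mixed model with baseline as a response is a standard choice and is unbiased under randomisation. The affected outcomes are declared exploratory, and no confirmatory conclusion rests on them. Adjustment is planned as a sensitivity analysis, and the unnamed covariates could include the baseline value. Section 4.1 also allows covariate-adjusted generalised linear models for α-diversity. Stratification by stage and age already limits chance T0 imbalance for stage-related outcomes, which the formula ignores. And the gain depends on a correlation that the article does not give.

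Most of this stands as a limit on the point. It does not remove it. The main model is fixed in the text and leaves baseline out of the adjustment; a sensitivity analysis does not change the main estimate. Exploratory status is a weak defence when these outcomes exist chiefly to yield effect sizes.

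A reader might infer three stronger things, and the article supports none of them:

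- **That the primary test loses efficiency.** Section 4 does attach the primary label to the C versus D change, but section 4.1 tests the Bray–Curtis endpoint by PERMANOVA, to which neither the variance ratio nor the fix applies.
- **That the planned estimates are biased by regression to the mean.** A chance T0 imbalance can shift a realised estimate, but over randomisations this is the same noise already counted in the variance.
- **That the gain is large and free for every outcome.** It is about 4–5% of variance at ρ = 0.9, and adjustment costs about one degree of freedom.

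**Conclusion.** The point holds as one of efficiency, confined to the continuous outcomes analysed by the linear mixed model. For these, baseline adjustment would reduce the variance of the C versus D contrast at T1 by about 34%, 24%, 14% and 4% at ρ = 0.3, 0.5, 0.7 and 0.9, net of the degree-of-freedom cost. The figures assume equal variances at T0 and T1, a linear relation, complete data and no allowance for stratification. The outcomes differ in kind, so no single value of ρ will represent them all. The planned analysis remains valid. The change is worth making because precise effect sizes are the pilot's stated aim and the T0 values are already collected.

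**What to change.** For the continuous outcomes in the mixed model, specify one of two forms as the main analysis and take C versus D at T1 from it:

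1. Model T1, FU1 and FU2 as responses, with the T0 value and T0 × time as covariates.
2. Keep T0 as a response but give all arms a common T0 mean, by dropping the diet, exercise and diet × exercise terms at T0. Use an unstructured covariance over time in place of a random intercept alone.

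The two are not interchangeable. The first drops participants with no value after T0; the second keeps them, which sits better with the intention-to-treat principle stated in section 4. The text should also say that the PERMANOVA analysis of the primary endpoint is unchanged.

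The cost is a revised model specification before analysis, about one degree of freedom in the covariate form, and a few more covariance parameters in the constrained form. No extra data, visits or participants are needed.

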**FIGURE 2 F2:**
[figure not shown]
Organization of the intervention study. T0, baseline (week 0); T1, end of intervention (week 24); FU1, first follow-up (week 36); FU2, second follow-up (week 48).

T0 (baseline): pre-intervention assessment (Week 0)T1 (end of intervention): 6 months after the start of the intervention (Week 24)FU1 (first follow-up): 3 months post-intervention (Week 36)FU2 (second follow-up): 6 months post-intervention (Week 48).

This longitudinal design allows sufficient time to characterize temporal changes in GM composition and diversity (Clauss et al., 2021; Pagliai et al., 2020).

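### As written, the four-visit mixed model implies one variance and one correlation for visits 12 to 48 weeks apart; if correlation decays with time, the intervals on some durability contrasts have the wrong width

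*Protocol article*

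**What the plan says.** Section 4 (Statistical analysis) says that "outcomes measured repeatedly over time will be analyzed using mixed-effects models to account for within-participant correlation". For continuous outcomes, "linear mixed-effects models will include fixed effects for time, diet, exercise, and their interactions" (or time by trial arm), "and a random intercept for participant". It names no random slope, residual covariance or robust standard error.

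The Figure 2 legend in section 3.4.1 fixes the visits: "T0, baseline (week 0); T1, end of intervention (week 24); FU1, first follow-up (week 36); FU2, second follow-up (week 48". The six visit pairs are therefore 12, 12, 24, 24, 36 and 48 weeks apart.

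On status, section 4 states: "The prespecified primary contrast will focus on the change from T0 to T1 in the combined intervention versus standard care (control", while "analyses including FU1 and FU2 will be considered secondary/exploratory and reported as durability/maintenance assessments". Section 4.1 tests the primary Bray–Curtis endpoint for Group C against "standard care (Group D) using Permutational Multivariate Analysis of Variance (PERMANOVA", not with the mixed model. Section 3.5.2 calls all secondary clinical and biomarker outcomes exploratory and says that they are meant mainly to give feasibility metrics and effect sizes for a definitive trial.

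**The concern.** A random intercept with independent residuals has two variance parameters. It gives every visit the same variance and every pair of visits the same correlation, so a participant's values at weeks 0 and 48 are taken to be as closely related as those at weeks 24 and 36. With complete balanced data, every change contrast then gets the same standard error, whichever two visits it compares.

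In a progressive disease, with an intervention that stops at week 24, falling correlation over longer gaps is at least plausible. The common standard error would then be too small for long gaps and too large for short ones. Change from baseline to FU1 or FU2 would look more precisely estimated than it is. Change from T1 to FU1, the first look at what happens after the intervention ends, would look less precise than it is. Effect estimates with their uncertainty are what these outcomes are meant to hand on to a later trial, so interval width matters even without a confirmatory test.

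**Working it through.** **Plan's own figure.** The protocol states no correlation, variance or standard error for this model, so there is nothing to reproduce.

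**Inputs.** Visits at weeks 0, 24, 36 and 48 (Figure 2 legend), and the random-intercept model (section 4). Assumed, because the documents are silent: correlation falls by a factor r per 12 weeks, with r = 0.6, 0.7 or 0.8 and constant variance. Visit-level measurement noise has variance k times the decaying variance, with k = 0, 0.5 or 1.

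**Formula.** With a decaying variance of 1, half the variance of a change over gap g weeks is h = 1 − r^(g/12) + k. The model replaces each h by its mean over the six pairs, so

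model SE / true SE = √(mean h / h), and two-sided error of a nominal 5% test ≈ 2·(1 − Φ(1.96 × ratio)).

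A stable participant component cancels from every change, so it does not alter the ratios.

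**Worked example, r = 0.8, k = 0.** The pairwise correlations are 0.8, 0.8, 0.64, 0.64, 0.512 and 0.4096. Their mean is 3.8016/6 = 0.6336, so mean h = 0.3664.

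- T0–T1: √(0.3664/0.36) = 1.01
- T0–FU1: √(0.3664/0.488) = 0.87
- T0–FU2: √(0.3664/0.5904) = 0.79
- T1–FU1: √(0.3664/0.20) = 1.35
- T1–FU2: as T0–T1, 1.01

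**Same r, k = 1.** Mean h = 1.3664. T0–FU1: √(1.3664/1.488) = 0.96. T0–FU2: √(1.3664/1.5904) = 0.93. T1–FU1: √(1.3664/1.20) = 1.07.

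**Range** (r = 0.6 / 0.7 / 0.8):

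| Contrast | Gap (weeks) | k = 0 | k = 0.5 | k = 1 |
|---|---|---|---|---|
| T0–T1, T1–FU2 | 24 | 0.99 / 1.00 / 1.01 | 0.99 / 1.00 / 1.00 | 0.99 / 1.00 / 1.00 |
| T0–FU1 | 36 | 0.89 / 0.88 / 0.87 | 0.94 / 0.93 / 0.94 | 0.95 / 0.95 / 0.96 |
| T0–FU2 | 48 | 0.85 / 0.82 / 0.79 | 0.91 / 0.89 / 0.89 | 0.93 / 0.93 / 0.93 |
| T1–FU1 | 12 | 1.25 / 1.30 / 1.35 | 1.12 / 1.12 / 1.11 | 1.08 / 1.08 / 1.07 |

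The error of a nominal 5% test for T0–FU2 is 0.10–0.12 with no noise and about 0.07 at k = 1. For T1–FU1 it is about 0.01 with no noise and about 0.035 at k = 1.

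**Simulation check.** REML fits to simulated data (18 per arm, r = 0.8, no noise) gave 1.007 for T0–T1, 0.865 for T0–FU1 and 0.786 for T0–FU2, in line with the formula.

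**Other patterns for T0–T1.** A random slope (variance 0.06 per 12 weeks squared) gave a four-visit ratio of 1.05. With r = 0.8 and an SD growing from 1.0 to 1.3 it was 1.105. If slope variance dominates, the squared gaps in 12-week units are 4, 9, 16, 1, 4 and 1, with mean 35/6 = 5.83, and the ratio tends to √(5.83/4) = 1.21. A fit to T0 and T1 alone gave about 1.00 in both simulated cases (r = 0.8, and random slope).

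**Constant correlation and variance.** All ratios are exactly 1.

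**The case against.** The protocol names a random intercept but does not say that it is the only structure or that residuals are independent. A residual covariance can sit beside a random intercept, and an article may leave that to an analysis plan that is not shown. This stands as a limit: the point concerns the model as stated, and the analysis plan may already go further. It does not remove the point, because the article does state a within-participant structure, and that structure followed literally has the consequence shown.

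No correlation is documented, and the no-noise column is an extreme. The outcomes in section 3.5.2 are rating scales, questionnaires, gait measures and assays, where visit-level error is expected and shrinks the effect. This stands, and it is why the range includes noise.

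The affected analyses are exploratory, and section 4 ties the 0.05 threshold to the prespecified primary analysis. With complete balanced data the point estimates do not depend on the covariance choice. This also stands and limits the consequence to interval width.

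A reader might infer that both errors push towards a finding of maintained benefit. The figures do not support that as a general statement. T1–FU2 is also a durability contrast, and under constant-variance decay its standard error is about right, so loss of effect by FU2 would not be hidden.

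**Conclusion.** The point holds conditionally and is modest. As stated, the model assumes equal variance and equal correlation across unequally spaced visits. If correlation decays by 0.6–0.8 per 12 weeks, with noise from none to equal to the decaying variance, standard errors are about 4–13% too small for T0–FU1, 7–21% too small for T0–FU2 and 7–35% too large for T1–FU1.

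Three stronger readings are not supported. First, the standard errors are not known to be wrong: with constant correlation and variance they are right, and the documents do not say which case applies. Second, T0–T1 is not safe in general. It is nearly right under constant-variance decay because a 24-week gap lies close to the average, but in a four-visit fit it was 5–11% too large with random slopes or growing variance. Third, the primary result is not affected, since the Bray–Curtis contrast is tested by PERMANOVA. What is at stake is the width of intervals on secondary and durability effect estimates.

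**What to change.** In section 4, replace the random intercept for continuous outcomes with an unstructured within-participant covariance over the four fixed visits, with Satterthwaite degrees of freedom. State a fallback: if the model does not converge, keep the random intercept and use participant-clustered robust standard errors. A Toeplitz structure is not a suitable fallback, because it works by visit order and would treat the 24-week T0–T1 gap and the 12-week T1–FU1 gap as equal. It would also help to say whether the T0–T1 contrast comes from a two-visit or a four-visit fit.

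The cost is a sentence or two of text. The unstructured form has 10 covariance parameters (4 variances and 6 covariances) against 2, for 80 participants, and loses a little precision if the correlation is in fact constant.
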